### Data collection

2.5

The midwives and doctors involved at the time of enrolment will collect socio-demographic data, with the help of a pre-structured form, to which a unique alphanumeric code will be attributed. The socio-demographic data collection form and the data collected during the course of the study will be stored separately. The parameters requested from the women will be (1): date of birth (2), expected date of delivery, (3) educational qualification, (4) occupation, (5) marital status, (6) number of pregnancies and deliveries, and (7) partner’s occupation, if any.

The woman will also be asked if she would like to participate in a qualitative interview (see Appendix 2 for the interview structure) two months after the birth. If she agrees, she will be asked for a telephone number to be contacted again. Women who give consent to this interview will be sent (again via the app) a questionnaire one month after the expected date of birth in which the following will be asked: [1] actual date of birth, [2] sex of the child, [3] name of the child, and [4] date and time the woman wishes to be contacted for the interview. Finally, the woman will be offered the use of the smartwatch as an optional choice.

Overall, as shown in **Table 1**, the psychoeducational course involves the completion of self-report questionnaires, which are delivered at the beginning, during and at the end of the interaction with REA. The instrument’s completion time is approximately 15 minutes.

Specifically, 4 questionnaires will be administered at the beginning and at the end of the psychoeducational intervention to investigate depressive symptoms, psychological flexibility and quality of life. None of these questionnaires have a diagnostic purpose, so they will not be used to diagnose psychopathology but only to collect descriptive data. Women with psychopathology will be excluded *a priori* from participation in the study (as defined in the Exclusion Criteria section).

A further 4 questionnaires will be sent out during the course to analyze the usability and engagement of the woman with the app and the virtual coach, REA.

The Whooley questions (24) are based on two PHQ-9 (34) items with a yes/no answer mode, administered by the practitioner; a positive test is defined as a positive answer to even one question. The questions are: During the last month, have you often felt down, depressed or hopeless? Have you often felt little interest or pleasure in doing things in the last month?

In pregnancy, for the identification of ‘mixed’ depression the instrument has 100% sensitivity with 68% specificity. In the postnatal period, sensitivity is 100% with specificity 64% for ‘mixed’ type depression and 100% and 44% respectively for major depression.

The Centre for Epidemiological Studies-Depression Scale (CES-D) (25) is a 20-item measure that asks carers to rate how often in the last week they have experienced symptoms associated with depression, such as restless sleep, poor appetite and feelings of loneliness. Response options range from 0 to 3 for each item (0 = rarely or not at all, 1 = sometimes or a little, 2 = moderately or a lot, 3 = most of the time or almost always). Scores range from 0 to 60, with high scores indicating major depressive symptoms. Being an epidemiological instrument, it is particularly short; in fact, the administration takes about ten minutes.

The Multidimensional Psychological Flexibility Inventory (MPFI) (26) is an assessment tool that measures psychological flexibility on several dimensions. It investigates how people adapt their thoughts and behaviors in response to changing situations and challenges. The MPFI focuses on various aspects of psychological flexibility, including openness to experiences, present-moment awareness, and value-driven action. The 12 dimensions of flexibility and inflexibility (according to the Hexaflex model) are assessed through 60 Likert scale items from 1 to 6. The Italian adaptation of the MPFI scale was developed by Landi et al. (35).

The 12-Item Short Form Survey (SF-12) (27) consists of 12 items (taken from the 36 items of the original SF-36 questionnaire (36)) that produce two measures relating to two different aspects of health: physical health and mental health. The SF-12 consists of 4 scales (physical functioning, role and physical health, role and emotional state, mental health) each measured by 2 items and 4 scales each measured by 1 item (physical pain, vitality, social activities and general health). The subject is asked to respond about how he or she feels and how well he or she is able to perform usual activities, evaluating the day on which he or she completes the questionnaire and the previous 4 weeks.

The Italian Version of the Chatbot Usability Scale, version B (ITA BUS B) (28), is designed to assess users’ ease of use, effectiveness, and satisfaction in interacting with chatbots. This tool is structured around 11 items that cover various aspects of the user experience with chatbots, aiming to provide an in-depth, multidimensional assessment of their usability. The items involve responses on a 5-point Likert scale, where 1 equals “strongly disagree” and 5 equals “strongly agree” thus scoring from 11 to 55.

The System Usability Scale (29) is a quick and reliable tool for assessing system usability. It consists of 10 items with Likert-type responses from 1 to 5. The questionnaire, developed by Brooke, provides an overall score that reflects the ease of use and applicability of a system or product. This score can range from 10 to 50. A document with printable SUS questions is available online (37).

The User Engagement Scale Short-form (28) is a short self-report questionnaire to assess user engagement with a digital solution. This measure includes 12 items based on a 5-point Likert scale, ranging from 1 (strongly disagree) to 5 (strongly agree). The questionnaire consists of 4 factors: (1) focused attention, which indicates the feeling of being immersed in the interaction; (2) perceived usability, which is the negative effect experienced due to the interaction and the effort expended; (3) aesthetic attractiveness, which represents the graphical and visual appeal to a digital solution; (4) the reinforcement factor (reward). The latter is a single factor that includes duration, which evaluates the overall success of the interaction; novelty, which examines the general interest related to the interaction with a digital solution; and, finally, the perceived engagement factor, which evaluates the overall enjoyment of the interaction. This questionnaire was not translated into Italian and was, therefore, translated through the Back Translation procedure.

The User Mobile Application Rating Scale (31) is a tool for assessing the quality of mobile apps and its functionalities. It is characterized by a 20-item measure that includes 4 objective quality subscales (engagement, functionality, aesthetics, and information quality) and 1 subjective quality subscale rated on a 5-point Likert scale, ranging from 1 (poor) to 5 (excellent). The total and subscales scores have very high Cronbach alpha coefficients (.90 and.78-.80, respectively). The scale has been also validated in an Italian context (38).

Psychologists from the project team will conduct the interviews. The interviews are structured with *ad hoc* items to purposively capture specific characteristics of the study and participants’ experiences (39). This interview will be carried out two months after the birth, will last approximately 20 minutes and, with the woman’s consent, will be audio-recorded to allow subsequent analysis.

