**Expected results:**

The intervention is expected to demonstrate high levels of user satisfaction and engagement (SUS ≥ 68, UES-SF ≥ 3,5/5; ITA BUS B ≥ 44/55 (≈4,0/5); uMARS ≥ 4,0/5), resulting in improvements in psychological flexibility, perceived well-being, and overall quality of life, recognizing that preventive efficacy will be evaluated in subsequent studies with controlled designs and postpartum outcome measures.

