#### Primary outcomes

2.4.1

The primary outcomes are UX and UE. They will be assessed via questionnaires, namely the User Engagement Scale Short-form (UES-SF) (28), the System Usability Scale (SUS) (29), the Italian version of the Chatbot Usability Scale (ITA BUS B) (30), and the User Mobile Application Rating Scale (uMARS) (31), which will be administered at different time slots through the study, in particular the usability questionnaires will be administered at the end of the third (3 questionnaires) and sixth (end of the study; 4 questionnaires) weeks.

The endpoints to be measured are as followed:

- Scores of the individual items of the questionnaires;- Mean score of the questionnaires;- Differences between the average score values of the individual questionnaires at the different survey times.

The experience of using the app and the virtual coach (REA) and using the intervention itself will be assessed through a semi-structured interview. The endpoints to be measured are qualitative.

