## Expected results

3

The psychoeducational pathway is expected to yield significant results, primarily in terms of women’s satisfaction and engagement with the use of the innovative digital solutions (SUS ≥ 68; average UES-SF ≥ 3.5/5; ITA BUS B ≥ 44/55; uMARS ≥ 4/5). Thresholds for usability and engagement were pre−specified based on established interpretive benchmarks and validated scale ranges: SUS ≥68 reflects above−average usability; UES−SF ≥3.5/5 indicates engagement above the neutral midpoint; ITA BUS B ≥44/55 corresponds to an average item agreement of ≥4/5; and uMARS ≥4/5 denotes high app quality. These targets are consistent with guidance and validation for the respective instruments (28–31).

We anticipate an increase between pre- and post-intervention in the levels of psychological well-being, quality of life of the woman and psychological flexibility. Specifically, we hypothesize: (i) an increase in MPFI psychological flexibility, (ii) an improvement in the mental component of the SF-12, (iii) a reduction in CES-D. These outcomes are exploratory and consistent with the main objective of assessing the acceptability, feasibility, and UX/UE of the intervention. It is important to highlight that, on the one hand, REA can be a valuable resource in ensuring regular psychoeducational support for women during the perinatal period. On the other hand, the literature has shown that women during the perinatal period indicated a preference for support provided online, suggesting that the implementation of digital interventions can overcome barriers around social stigma and reluctance to seek help.

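### The SUS is described as scoring 10 to 50, but its pre-specified target is SUS ≥ 68, which the mean cannot reach on the scale as written

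*Protocol article*

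**What the plan says.** Section 2.5 (Data collection) says of the SUS: "It consists of 10 items with Likert-type responses from 1 to 5". It then describes an overall score and gives its limits: "This score can range from 10 to 50".

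The abstract, under Expected results, gives the targets beginning "SUS ≥ 68, UES-SF ≥ 3,5/5". Section 3 (Expected results) repeats them as "SUS ≥ 68; average UES-SF ≥ 3.5/5; ITA BUS B ≥ 44/55; uMARS ≥ 4/5" and explains the first: "SUS ≥68 reflects above−average usability". Section 3 also says where the targets come from: "Thresholds for usability and engagement were pre−specified based on established interpretive benchmarks and validated scale ranges".

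Section 2.4.1 makes the SUS a primary-outcome instrument: "The primary outcomes are UX and UE", assessed with the UES-SF, SUS, ITA BUS B and uMARS. The endpoints listed there are item scores, mean questionnaire scores, and differences in mean score between survey times. Table 1 places the SUS at the end of week 3 and at the end of the study.

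**The concern.** The target for one primary-outcome instrument lies outside the range that the same article gives for that instrument. Section 3 says the targets were chosen with the scale ranges in mind, so the article itself claims that range and target agree. For the SUS they do not.

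Two things are at stake. First, an analyst who scores the SUS as section 2.5 describes and compares the mean with 68 must report that the target was missed, however usable the app is. Second, an analyst who notices the mismatch has to choose a conversion that the article does not give. The plausible conversions lead to different thresholds, and section 2.7 schedules a preliminary analysis for early November 2025, so that choice could be made with data in hand.

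**Working it through.** **Inputs**
- SUS: 10 items, responses 1 to 5, stated range 10 to 50 (section 2.5).
- SUS target: ≥ 68 (abstract; section 3, twice).
- ITA BUS B, for comparison: 11 items, responses 1 to 5, stated range 11 to 55 (section 2.5); target ≥ 44/55, described as a mean item score of at least 4 (section 3).
- UES-SF and uMARS targets: 3.5/5 and 4/5 (abstract; section 3).

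**Step 1: reproduce the stated SUS range.** For an unweighted item sum, the minimum is items × lowest response and the maximum is items × highest response.
- Minimum: 10 × 1 = 10.
- Maximum: 10 × 5 = 50.

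This matches section 2.5 exactly, so the stated range is that of a plain item sum.

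**Step 2: compare with the target.**
- Shortfall: 68 − 50 = 18 points.
- Mean item response needed: 68 / 10 = 6.8, against a maximum of 5.

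A mean of scores that cannot exceed 50 cannot exceed 50, so the target is unreachable on this scale for any sample.

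**Step 3: check the other three targets.**
- ITA BUS B: 11 × 1 = 11 and 11 × 5 = 55, as stated; 44 / 11 = 4.0, as stated. Range and target agree.
- UES-SF and uMARS: both targets are given out of 5 and lie below 5.

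Only the SUS target has no stated denominator, and only the SUS target exceeds its range.

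**Step 4: what 68 could mean on the 10-50 scale.** The article gives no conversion, so both lines are assumptions.
- Linear map of 10-50 onto 0-100: score = (sum − 10) × 2.5, since 100 / (50 − 10) = 2.5. Solving for 68: sum = 68 / 2.5 + 10 = 27.2 + 10 = 37.2, a mean item score of 3.72.
- 68 per cent of the maximum: 0.68 × 50 = 34, a mean item score of 3.4.

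The two readings differ by 37.2 − 34 = 3.2 points on the 10-50 scale.

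**Step 5: effect on the change endpoint.** Under the linear map, a difference between week 3 and the end of the study is 2.5 times as large on 0-100 as on 10-50. A paired test on the same totals is unchanged by that rescaling; only the size of the reported difference depends on the scale.

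**The case against.** The best reply is that this is one wrong descriptive sentence with limited consequences. Much of that stands.

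- A reader might infer that ≥ 68 is the trial's formal success criterion and that the study is bound to fail. The article does not support this. Section 2.4.1 defines the primary endpoints without any threshold, section 2.7.1 does not use one, and no decision to proceed or stop is tied to it. The figure stands under Expected results as an anticipated level.
- A reader might infer that every participant is classed as failing. Nothing in the article applies 68 to individuals or defines a responder proportion. The natural comparison is with the mean.
- A reader might infer that any correction would be a post hoc change of target. Section 3 already ties 68 to above-average usability on an established benchmark. If the range sentence is the error, correcting it brings the scoring into line with that benchmark and does not move the target.
- The sample size in section 2.6 does not use the SUS threshold, and data collection is untouched.

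The reply does not remove the contradiction. Both figures stand in plain prose, and the range is reproduced exactly by the item count. The point is therefore two stated figures that conflict, not a scoring detail left to a fuller document. Section 3 also describes the targets as pre-specified, so they will be read as yardsticks for the results.

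**Conclusion.** The contradiction is real and rests on the article's own numbers: a stated maximum of 50 against a target of 68, a gap of 18 points, for one of the four primary-outcome instruments. As written, the mean SUS cannot meet its pre-specified benchmark. The consequence is confined to interpreting the SUS result against that benchmark and to the scale on which the SUS mean and its change are reported.

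The likely explanation is that section 2.5 gives the raw item-sum range while 68 belongs to a 0-100 score. The article does not say so. Nor does it mention a multiplier or reverse-scored items. The equivalents of 37.2 and 34 are therefore conditional on the conversions assumed above, and they take the item sum to be one in which higher always means more usable.

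**What to change.** Before the data are read, state one SUS scoring rule and its range in section 2.5, taken from the instrument source the article cites. This should include how individual items enter the total. Then express the threshold on that same scale, with its denominator, in the abstract and section 3.

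- If the source confirms that 68 is on a 0-100 score, replace the 10-50 sentence with that score and keep ≥ 68.
- If the 10-50 total is kept, restate the threshold on it and name the conversion used: 34 if 68 means 68 per cent of 50, or 37.2 under the linear 0-100 map.

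Report the week 3 and end-of-study SUS means, and their difference, on the chosen scale.

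The cost is about one sentence in section 2.5 and a denominator beside the threshold elsewhere (or a restated threshold if 10-50 is kept). Data collection and sample size do not change.

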### Sample size

2.6

The present research project is a proof-of-concept study, in which a limited sample is sufficient to achieve the intended aims.

If non-parametric statistics are conducted (assuming that the distribution is not normal), the sample should consist of N = 24 pregnant women with Bonferroni correction (α = .025).

The sample size and power for nonparametric tests (Kruskal-Wallis Test, Wilcoxon *post-hoc* test) were calculated according to Noether (40).

If parametric statistics are conducted (assuming that the distribution is normal), the sample must instead consist of 41 pregnant women with Bonferroni correction (α = .025).

Therefore, setting the power level at.80 and the significance level at.025 and taking into account a 20% possible drop-out, a total of 50 pregnant women were estimated to need to be recruited in order to carry out the study.

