#### Quantitative analysis

2.7.1

Statistical data processing will be conducted via R software, version 4.0.0 (RStudio Team, 2020), IBM SPSS Statistics (IBM Corp, 2020), Stata17 (StataCorp, 2021), and JASP (Jasp Team, 2024).

Categorical variables will be summarized through absolute and percentage frequency distributions, and quantitative variables through appropriate centrality and variability indices.

Descriptive analyses will be calculated for both the psychological variables (depressive symptoms, psychological flexibility and quality of life) and the usability (UX) and user involvement (UE) variables. These analyses will be performed on the variables analyzed at the beginning, during and at the end of the interaction with REA.

The relationships between variables will be analyzed mainly through *ad-hoc* statistical tests, such as the chi-square test, Fisher’s exact test, t-test for paired data or Wilcoxon’s nonparametric tests and the sign test (based on an assessment of compliance with assumptions) to understand the differences between the beginning and the end of the path in the same study sample to the variables under investigation.

In addition, univariate logistic or multinomial regression models will be presented. Finally, to eliminate possible confounding factors, multiple regression models will be proposed in which the effects of the explanatory variables on the outcome variables will be adjusted for possible confounders. For each analysis, statistical significance will be found with a p-value ≤.05.

Multivariate models will include adjustment for potential confounders collected in the protocol, including maternal age, educational attainment, employment status, marital status, previous pregnancies/births (parity), gestational age at enrolment, baseline CES-D, MPFI and SF-12 scores. The extant literature identifies these variables as being associated with perinatal mental well-being and adherence to digital solutions. Sensitivity analyses will explore the robustness of the results with respect to different model specifications and the availability of wearable data (steps, sleep, HR) as exploratory covariates.

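### The .80 power in section 2.6 is not tied to any endpoint: it cannot cover usability scales measured once, and it is not stated for the four primary means set against the section 3 thresholds

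*Protocol article*

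**What the plan says.** Section 2.4.1 states: "The primary outcomes are UX and UE". They are measured with UES-SF, SUS, ITA BUS B and uMARS. It lists three quantitative endpoints: item scores, mean scores, and differences in mean score between survey times. It counts three usability questionnaires at the end of week 3 and four at the end of week 6. Table 1 shows only two at week 3 (SUS and ITA BUS B), with UES-SF and uMARS at week 6 alone.

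Section 2.6 says that "a limited sample is sufficient to achieve the intended aims". For the non-parametric case, "the sample should consist of N = 24 pregnant women with Bonferroni correction (α = .025"), and "The sample size and power for nonparametric tests (Kruskal-Wallis Test, Wilcoxon *post-hoc* test) were calculated according to Noether (40"). For the parametric case, "the sample must instead consist of 41 pregnant women with Bonferroni correction (α = .025"). The total of 50 follows from "setting the power level at.80 and the significance level at.025 and taking into account a 20% possible drop-out". No endpoint, effect size, SD, sidedness or precision target is given.

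Section 2.7.1 names paired t, Wilcoxon and sign tests for change from beginning to end, association tests and regression models. Section 3 sets pre-specified thresholds: SUS 68, UES-SF 3.5/5, ITA BUS B 44/55 and uMARS 4/5, the last explained as "uMARS ≥4/5 denotes high app quality". Section 2.5 gives the SUS score a range of 10 to 50.

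**The concern.** A power figure belongs to a particular test of a particular endpoint at a particular effect size. Section 2.6 attaches .80 to the study as a whole and says the sample is enough for its aims. The primary aim has at least two quantitative readings: change between survey times, and the level of each scale, for which section 3 supplies the only numerical targets in the article. A comparison-test power can speak to the first reading, and only for scales measured twice. Nothing in section 2.6 speaks to the second.

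What is at stake is how firmly the report can say that a usability or engagement target was reached. A reader who sees .80 power beside four pre-specified thresholds could take it that the study is powered to judge them. The article neither claims nor supports that.

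**Working it through.** **1. The plan's own figures.** They cannot be derived from the article, which gives no effect size, so I solved backwards.
- Parametric: paired or one-sample t-test, two-sided α = .025, power .80, *assumed* standardised effect d = 0.5. The normal approximation is (2.241 + 0.842)²/0.5² = 9.505/0.25 = 38.0, so 39. Exact noncentral-t power is 0.793 at n = 40 and 0.805 at n = 41. So n = 41, as stated.
- Non-parametric: Noether's signed-rank formula, n = (z_α + z_β)²/[3(p − 0.5)²]. Setting n = 24 gives p = 0.5 + √(9.505/72) = 0.863, which corresponds to d of about 0.8. At d = 0.5 the same formula gives 47.
- Total: 41 × 1.2 = 49.2, so 50. A 20% loss from 50 leaves 40.

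The exact match at 41 fits a paired change test, but a one-sample test gives the same n, so the endpoint that was sized remains an inference.

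**2. What that power can cover.**

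| Scale | Week 3 (Table 1) | Week 6 | Within-woman change test possible |
|---|---|---|---|
| SUS | yes | yes | yes |
| ITA BUS B | yes | yes | yes |
| UES-SF | no | yes | no |
| uMARS | no | yes | no |

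If the section 2.4.1 count of three at week 3 governs, one of the last two rows becomes yes and a single scale is left without a change test.

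**3. Precision against the thresholds, n = 40.** The 95% CI half-width is t(.975, 39)/√40 × SD = 2.023/6.325 × SD = 0.320 × SD. The article gives no SDs, so all SDs here are assumptions.

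| Scale | Threshold | Assumed SD | Half-width |
|---|---|---|---|
| SUS (0-100) | 68 | 12 / 15 / 20 | 3.8 / 4.8 / 6.4 |
| ITA BUS B (11-55) | 44 | 5 / 9 | 1.6 / 2.9 |
| UES-SF | 3.5 | 0.5 / 0.9 | 0.16 / 0.29 |
| uMARS | 4 | 0.5 / 0.9 | 0.16 / 0.29 |

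**4. Two ways of reading a threshold, SUS, n = 40.**
- If the observed mean alone is compared with 68, a true mean of 66 reaches it with probability 1 − Φ(2/(SD/√40)) = 0.15, 0.20 and 0.26 for SD 12, 15 and 20. A true mean of exactly 68 reaches it half the time.
- If the lower 95% limit must reach 68, a true mean of 72 succeeds with probability 0.54, 0.38 and 0.23 for the same SDs.

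**The case against.** The strongest reply is that change between survey times is itself a listed primary endpoint, so a change-test calculation does address part of the primary aim. That stands. The fault is that section 2.6 does not say so, and that such a calculation cannot reach a scale measured once.

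A reader might go further and infer that exactly half of the primary scales lack a change test. Table 1 supports this, but section 2.4.1's count of three questionnaires at week 3 contradicts it, so the number is open until the two are reconciled.

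A reader might infer that each threshold is passed or failed on the observed mean. No such rule is written. The thresholds stand under expected results in an exploratory proof-of-concept study, and no decision is made to depend on them. The pass rates in step 4 describe one possible reading, not the plan.

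A reader might also infer that the sample size carries no information on the thresholds. Numerically it does: 41 completers give 80% power for a one-sample test when the true mean lies 0.5 SD above the threshold. The article neither states nor uses this.

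Finally, the list of tests in section 2.7.1 is open-ended, and interval reporting is often left to an analysis plan. That is fair, and the missing interval alone would not be a finding. The point rests on section 2.6, which states a power and a claim of sufficiency without tying either to an endpoint.

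**Conclusion.** The point holds in this form: the .80 power is unattached. It can at most cover change in SUS and ITA BUS B (plus one further scale if section 2.4.1 governs). It cannot cover scales measured once, and it is not stated for the comparison of the four primary means with their thresholds. For that comparison the useful figure is precision, a 95% CI half-width of about 0.32 SD with 40 completers. An observed SUS mean within about 4 to 6 points of 68 would therefore leave the threshold inside the interval.

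This rests on 20% loss from 50, on the assumed SDs, and on 0-100 SUS scoring. The last matters because a threshold of 68 cannot be reached on the 10 to 50 range given in section 2.5. Nothing here shows that 50 women are too few for a proof-of-concept study. The correction concerns what the sample size is said to support.

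**What to change.** - **Section 2.6:** name the endpoint, test and effect size to which the .80 power applies, and limit the claim to them. For the thresholds, state the expected precision: about 40 completers, 95% CI half-width about 0.32 SD, with the assumed SD of each scale.
- **Section 3 or 2.7.1:** report each week-6 mean with its 95% CI beside its threshold. Describe a threshold as clearly exceeded only when the whole interval lies above it. Do not make the lower limit a compulsory success rule: at this size it would often fail an app truly 4 SUS points above target (step 4).
- **Section 2.4.1 and Table 1:** reconcile the number of questionnaires at week 3, and say which scales have a change endpoint.
- **Section 2.5 and section 3:** reconcile the SUS score range with the threshold of 68.

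The cost is a few sentences and a routine interval, with no additional women or data. The price is softer wording when a mean falls only just above its threshold.

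### Section 2.6 misstates two parts of its sample-size justification: 50 recruited less 20% leaves 40 rather than the stated 41, and the non-parametric N = 24 is attributed to a Kruskal-Wallis test that does not fit a single-group pre-post design

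*Protocol article*

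**What the plan says.** The Sample size section (2.6) of the Protocol article gives two alternative sizes. For non-normal data, "the sample should consist of N = 24 pregnant women with Bonferroni correction (α = .025"). For normal data, "the sample must instead consist of 41 pregnant women with Bonferroni correction (α = .025"). Both are followed by "setting the power level at.80 and the significance level at.025" and by the recruitment target: "taking into account a 20% possible drop-out, a total of 50 pregnant women were estimated to need to be recruited".

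The method for the smaller figure is introduced with "The sample size and power for nonparametric tests (Kruskal-Wallis Test, Wilcoxon" and credited to Noether, with the Wilcoxon test described as post-hoc. No effect size, standard deviation, endpoint or sidedness accompanies either figure.

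The Quantitative analysis section (2.7.1) compares the start and end of the programme within one sample. For this it names, among other tests, the "t-test for paired data or Wilcoxon’s nonparametric tests and the sign test", with the choice depending on a check of assumptions. Kruskal-Wallis does not appear there. The Limitations section (4.1) confirms that there is no control group.

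**The concern.** Two things in this paragraph do not fit together.

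First, the recruited number is meant to absorb a 20% loss and still meet the requirement at the stated power. Taking 20% off 50 does not leave 41.

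Second, the only named basis for the non-parametric size is a comparison of independent groups followed by post-hoc tests. The study has one group measured repeatedly. The resulting 24 is also far below 41 at the same significance level and power. If both came from one effect, the rank test would normally need slightly more women than the t-test, not about 40% fewer (1 − 24/41 = 41%).

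What is at stake is the accuracy of the stated power and whether a reader can rely on 24. Because section 2.7.1 picks the test after looking at the assumptions, the non-parametric route is a live option. If completion were poor, the text could be cited to say that 24 women were enough.

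**Working it through.** **Inputs from section 2.6:** 41 (parametric), 24 (non-parametric), α = 0.025, power 0.80, drop-out 20%, 50 to recruit. **Assumed, because not stated:** two-sided testing and the standardised change d (mean change divided by the SD of the changes).

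**1. Drop-out**
- Reproducing 50: 41 × 1.2 = 49.2, rounded up to 50.
- Evaluable women after a 20% loss: 50 × 0.8 = 40, one below 41.
- Correct inflation: 41 / (1 − 0.20) = 51.25, rounded up to 52.
- Loss that 50 can absorb: 1 − 41/50 = 18%.

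**2. Which effect gives 41?** Paired t-test (noncentral t), two-sided α = 0.025, power 0.80:

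| Assumed d | n |
|---|---|
| 0.4 | 62 |
| 0.5 | 41 |
| 0.6 | 29 |

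So d = 0.5 reproduces 41, though the article does not say that this was the effect used. A one-sided test at 0.025 with d = 0.45 also gives 41.

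**3. Cost of being one short.** At d = 0.5, power is 0.805 with 41 and 0.793 with 40. At the effect that gives exactly 0.80 with 41 (d = 0.497), power with 40 is 0.789. Either way the loss is about 1 percentage point.

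**4. Can 24 share an effect with 41?** Noether's formula for the signed-rank test is n = (z for α + z for power)² / [3(p′ − 0.5)²]. Here p′ is the probability that the sum of two independent changes is positive. For two-sided 0.025 and power 0.80 the squared term is 9.505.
- With normal differences and d = 0.5, p′ = 0.760, so n = 9.505 / (3 × 0.260²) = 46.8 (with unrounded p′), or 47.
- By asymptotic relative efficiency: 41 / 0.955 = 42.9, or 43.
- One-sided at 0.025 and d = 0.5: Noether gives 39 and the paired t-test 34, so the rank test is still the larger.
- Solving for n = 24: p′ = 0.5 + √(9.505/72) = 0.863, which is d ≈ 0.77 under normality. At that effect the paired t-test needs only 19.

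With normal differences, then, 24 and 41 cannot come from one effect.

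**5. Does non-normality rescue 24?** Simulated signed-rank power at a mean change of 0.5 SD, two-sided α = 0.025, n = 24:

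| Distribution of changes | Power |
|---|---|
| Normal | 0.51 |
| Laplace | 0.64 |
| t with 3 df | 0.78 |

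Power approaches 0.80 only with very heavy tails. The article asserts no such shape.

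**6. Test against design.** Kruskal-Wallis assumes independent groups. Section 4.1 rules out a control group, and section 2.7.1 compares two time points in the same women. Even the CES-D, which Table 1 schedules at baseline, at the end of the study and at follow-up, gives repeated measures rather than independent groups.

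**The case against.** The strongest reply is that none of this changes the study much, and most of that stands. The drop-out figure is a planning guess, the shortfall is one woman, and 50 still delivers 41 if 18% leave. This is a proof-of-concept study whose psychological changes are called exploratory.

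A reader might infer that 24 and 41 contradict each other. They do not: they are worded as alternatives, and 50 is built on the larger. Nothing permits recruitment to stop at 24, so a non-parametric analysis would also have about 40 women.

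A reader might also infer that 24 has been shown to be wrong and would leave roughly even odds of detecting the effect. The documents do not support that. The figures of 47 women and 0.51 power assume normal differences, while section 2.6 reserves 24 for non-normal data, where a rank test can need fewer women than a t-test. They also rest on a value of d that the article never gives.

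Finally, the sentence naming Kruskal-Wallis names Wilcoxon too, and the tests in section 2.7.1 are introduced as examples. Absence from that list is therefore not decisive by itself. The design is: with one group measured before and after, an independent-groups test has no place in the sizing.

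**Conclusion.** Two misstatements stand on the text. The allowance for 20% drop-out is computed wrongly, leaving 40 rather than 41. The non-parametric size is attributed to a test that does not suit the design. The first costs about 1 percentage point of power (about 0.79 instead of 0.80), if testing is two-sided and the unstated effect is near 0.5 SD. The second leaves 24 without support: it needs either a different effect from the one behind 41 or a very heavy-tailed distribution, and neither is given.

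It would go too far to say that the sample size fails or that the study is materially underpowered. The recruited number follows from 41, and neither 24 nor Kruskal-Wallis affects it. The severity is minor to moderate, and the remedy is wording.

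**What to change.** 1. Keep 50, but restate it as 40 completers after 20% drop-out with power slightly below 0.80 (about 0.79 if d is near 0.5), or as an 18% drop-out allowance. If the section is to keep both 20% and 41, the number to recruit is 52.
2. Remove Kruskal-Wallis and base the non-parametric size on the paired signed-rank test.
3. Drop N = 24 unless the sponsor states the effect and distribution behind it.
4. Have the sponsor state the effect size actually used for 41, with its endpoint and sidedness. The value 0.5 used here is a back-calculation and should not be written in as the design assumption unless the sponsor confirms it.

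If 50 is kept, the cost is a few sentences and a slightly lower stated power, with no change to recruitment or conduct. Choosing 52 means recruiting two more women.
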